The prediction of outcome after ankle fracture is relatively imprecise. We have previously shown that out of eight variables, pain and dorsiflexion range of motion soon after the period of immobilisation were the only independent predictors of outcome, but explained only 9 to 12% of the variance in activity limitation in the short- to medium-term [21]. Other variables (e.g. psychological factors) may be better predictors of outcome after ankle fracture. It has been shown that psychological variables (including pain catastrophising and depression) appear to be important predictors of outcome in people with other musculoskeletal conditions [22]. This issue has not been examined after ankle fracture.

The primary aims of the trial to be conducted are, therefore, to determine (a) the effectiveness and cost-effectiveness of rehabilitation, compared to simple advice and (b) if effects of rehabilitation are influenced by fracture severity or by the age and gender of participants. A secondary aim is to identify predictors of outcome after ankle fracture.

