### Statistical analysis

Analyses will be conducted by 'intention-to-treat' (i.e. all available data from all randomised participants will be analysed in the group to which the participant was allocated). Multiple imputation will be used for missing data. To test the effects of intervention on continuous outcomes (activity limitation, quality of life, return to pre-fracture work and leisure, physical activity (metabolic equivalent minutes per week), ankle range of motion, pain, walking speed, and global perceived effect of treatment), between-group comparisons will be conducted using longitudinal mixed models [30,31]. The independent variables will be a dummy-coded variable indicating group membership, the time at which the measurement was taken (four times, dummy-coded as three variables, with the baseline time as the referent category), and the three time-by-group interactions. The effect of rehabilitation at each of the three follow-up time points is estimated with the relevant interaction term. The model will incorporate random intercepts to account for the dependence of repeated measures. Survival analysis will be used to estimate between-group differences in days to pain-free walking and days to return to full pre-fracture work. Odds ratios will be calculated for physical activity (level), satisfaction with trial treatment, and adverse events.

In a second analysis, designed to test the influence of fracture severity on treatment response, additional terms (fracture severity and the interactions of fracture severity with the group and time variables) will be entered into the model. The effect of fracture severity on treatment response will be determined by examining the interactions between group membership, fracture severity and the time variables. A similar analysis will test the influence of participant age and gender on treatment response. Participants will be divided into women aged over 50 and others. Again, additional terms (age/gender and the interactions of age/gender with the group and time variables) will be entered into the model. The effect of age/gender on treatment response will be determined by examining the interactions between group membership, age/gender and the time variables.

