### Sample size

A sample of 76 participants (38 per group) would provide an 80% probability of detecting a difference between the group means of 10 points on the 80-point Lower Extremity Functional Scale (assuming a SD of 15 points, based on data from our recently completed trials [5,6]). This sample size will also provide 80% probability of detecting a difference between the group means of 2.75 points on the 45-point Assessment of Quality of Life scale (assuming a SD of 4 points, based on data from our recently completed trial [5]). Effects smaller than these are unlikely to be considered clinically worthwhile. In our calculations we assumed an alpha of 0.05, and we allowed for 5% loss to follow-up. We conservatively ignored the extra precision conferred by the longitudinal design.

In order to power the trial for analyses of the interactions with fracture severity and age/gender of participants we need to inflate the sample size by a factor of 2 + *k *+ 1/*k*, where *k *is the sub-group ratio. We anticipate the sub-group ratio for both *severe*: *less severe *fracture and *women aged over 50*: *others *is ~1:2 (based on our recently completed studies [5,6]). Thus, a sample of 72 × 4.5 = 342 participants (171 per group) will be recruited.

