## Discussion

The EXACT trial will provide evidence on the effectiveness of rehabilitation after ankle fracture. Participants receiving the *Rehabilitation *intervention will receive an individually tailored and exercise-based physiotherapy program and participants receiving the *Advice *intervention will not, because the intent is to compare the effects of these two alternatives when they are administered as usually applied in the clinic. We will not match the number of treatment sessions for the *Advice *group because, given the pragmatic orientation of the trial, it is more important to replicate current clinical practice. A pragmatic trial design [33,34] was chosen to enable easy translation of the research findings into clinical practice.

Our trial incorporates features that minimise bias, including concealed random allocation and blinded data analysis [35]. Blinding of outcome assessment may be particularly important in exercise trials such as ours, where the blinding of participants and therapists is not possible [36]. The primary outcomes (activity limitation, quality-adjusted life years etc) will be self-reported by participants who are not blinded. However the assessors who elicit primary outcome data, and who collect secondary outcome data such as ankle dorsiflexion range of motion and walking speed, will be unaware of group allocation. Consequently the assessment of outcome is partially blinded. Procedures recently suggested to achieve blinding in pragmatic physiotherapy trials will be used in our trial, including asking participants not to reveal their group allocation to assessors when booking follow-up appointments and at the start of each assessment, and restricting assessor access to trial data which indicates group allocation (computer files will be password protected and paperwork will be in a separate locked filing cabinet) [37]. We will also confirm the success of assessor blinding by asking the assessor if he or she was blinded to allocation and to guess which group the participant was allocated to after each assessment.

The sample size will be large enough to provide precise estimates of treatment effects. Importantly, the trial is adequately powered to investigate whether the effects of rehabilitation differ across sub-groups of participants [38]. In our trial we will determine if treatment effects are influenced by fracture severity and by the age and gender of participants.

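### The treatment and subgroup effects are unadjusted change-from-baseline contrasts, so the 80% power for the subgroup interactions holds only if the baseline-to-3-month correlation is at least about 0.5

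*Protocol article*

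**What the plan says.** The Statistical analysis section lists every fixed effect for the continuous outcomes: a group indicator, three time indicators with baseline as the reference, and three time-by-group products, with random intercepts for participants. It then says: "The effect of rehabilitation at each of the three follow-up time points is estimated with the relevant interaction term". It names no baseline covariate and does not constrain the arms to share a baseline mean. The two subgroup analyses (fracture severity; women over 50 against others) add the subgroup and its interactions, and read the subgroup effect from the group-by-subgroup-by-time terms. The primary conclusions on effectiveness and on both subgroup questions are drawn at 3 months.

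The Sample size section works from a two-group comparison of means: 76 participants "would provide an 80% probability of detecting a difference between the group means of 10 points", with an SD of 15. It adds: "In our calculations we assumed an alpha of 0.05, and we allowed for 5% loss to follow-up". On the repeated measures it says: "We conservatively ignored the extra precision conferred by the longitudinal design". The 76 is then multiplied by 2 + k + 1/k to power the interactions, although the sentence that does so reads: "Thus, a sample of 72 × 4.5 = 342 participants (171 per group) will be recruited". The Discussion concludes that "the trial is adequately powered to investigate whether the effects of rehabilitation differ across sub-groups of participants".

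**The concern.** The analysis and the sample size refer to two different estimators. The sample size describes a comparison of group means at one time. The model estimates a difference in change, which carries the noise of the baseline measurement as well as that of the follow-up. Such a contrast gains precision over a single-time comparison only when baseline and follow-up are correlated strongly enough. Otherwise it loses precision, and leaving the longitudinal design out of the calculation is not conservative.

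The subgroup interactions are where this matters. The main effect needed 76 participants. The increase to 342 was made solely for the interactions, which belong to the trial's primary aims, and they have almost no reserve if the variance is larger than assumed.

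**Working it through.** **Inputs** (Sample size section unless noted): LEFS difference 10, SD 15; Assessment of Quality of Life (AQoL) difference 2.75, SD 4; alpha 0.05 (taken as two-sided, which reproduces the plan's figure); power 80%; loss 5%; subgroup ratio 1:2. The correlation ρ is not in the document and is varied.

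**1. The plan's own figure.** LEFS per arm: 2 × [15 × (1.960 + 0.842)/10]² = 35.3, so 36; 36/0.95 = 37.9, so 38; total 76. AQoL needs 34 per arm, or 36 after loss, and is covered. Inflation with k = 0.5: 2 + 0.5 + 2 = 4.5, and 76 × 4.5 = 342. The printed product does not hold, since 72 × 4.5 = 324.

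**2. Interaction power as the plan assumes it.** Evaluable N = 342 × 0.95 = 324.9. SE = 15 × √(4 × 4.5/324.9) = 3.53. Power = Φ(10/3.53 − 1.96) = Φ(0.87) = 80.9%. For AQoL, SE = 0.94 and power is 83.2%.

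**3. What the planned coefficient estimates.** The fixed effects are saturated in group and time. With complete data the 3-month interaction term is therefore the difference in mean change from baseline, and the three-way term is the difference of two such differences. In simulated data sets at ρ = 0.3, 0.5 and 0.7, the fitted three-way coefficient equalled the hand-computed contrast (1.108, −2.373 and 1.841 both ways).

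**4. Variance of that contrast.** With equal variances σ² at both times, which the random-intercept model implies:

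- follow-up only: σ²
- change from baseline: 2(1 − ρ)σ²
- baseline-adjusted: (1 − ρ²)σ²

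The first two are equal at ρ = 0.5. The planned contrast has 2(1 − ρ)/(1 − ρ²) = 2/(1 + ρ) times the variance of the adjusted one: 1.54 at ρ = 0.3, 1.33 at 0.5, 1.18 at 0.7.

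**5. Interaction power, N = 324.9.**

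| ρ | LEFS, planned contrast | AQoL, planned contrast | LEFS, baseline-adjusted |
|---|---|---|---|
| 0 | 51.7% | 54.2% | 80.9% |
| 0.2 | 61.0% | 63.7% | 82.4% |
| 0.3 | 66.8% | 69.4% | 84.4% |
| 0.4 | 73.4% | 76.0% | 87.1% |
| 0.5 | 80.9% | 83.2% | 90.5% |
| 0.6 | 88.6% | 90.4% | 94.3% |
| 0.7 | 95.5% | 96.5% | 97.8% |

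Enrolment needed for 80% LEFS interaction power with the planned contrast is 4 × 4.5 × [15√(2(1 − ρ)) × 2.802/10]²/0.95: about 468 at ρ = 0.3, 402 at 0.4, 335 at 0.5 and 268 at 0.6.

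**6. Main effect.** At 342 enrolled, the planned contrast has 98.9% power for LEFS and 99.2% for AQoL even at ρ = 0.

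**The case against.** The strongest reply is that nothing in the protocol places ρ below 0.5. That stands. A reader might take the Background's remark that baseline predictors "explained only 9 to 12% of the variance in activity limitation in the short- to medium-term" as evidence of a correlation near 0.30 to 0.35, the square roots of 0.09 and 0.12. The figure does not support this. It is the variance explained by pain and dorsiflexion range, the two predictors retained out of eight, not by baseline LEFS. It does not estimate the correlation of LEFS with its own baseline.

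Two further replies have force. First, the protocol does not say whether 15 is the SD of scores or of change. If it is of change, the stated power stands. The wording, a difference between group means with the longitudinal design set aside, points to scores without settling it. Second, the 0.5 threshold depends on equal variances. In general it is SD at baseline divided by twice the SD at 3 months. Entry is restricted to stiff, painful ankles, so a smaller baseline SD is possible. With assumed SDs of 10 and 15 the threshold is 10/30 = 0.33. At ρ = 0.3 the change variance is 100 + 225 − 90 = 235, giving about 79% power, and at ρ = 0.4 about 84%.

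It is also fair to say that randomisation keeps the planned estimator unbiased, and that no type I error problem follows. None of this defends the choice of estimator itself: under the plan's own equal-variance model it is less precise than a baseline-adjusted one at every ρ below 1.

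**Conclusion.** The point holds as a conditional one and should be fixed. The planned estimator makes the interaction power depend on a correlation that the protocol neither states nor considers. LEFS power runs from 61.0% at ρ = 0.2 to 95.5% at ρ = 0.7 and reaches the claimed level only from about 0.5 upwards. This rests on reading 15 as an SD of scores, on equal variances at baseline and 3 months, and on a 10-point interaction with a 1:2 subgroup split.

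A reader might infer that the trial is underpowered, or that the statement about conservatism is false. The document supports neither. Both claims hold if ρ is high enough, so they are unassured rather than wrong. Nor is the main effectiveness comparison in doubt. The 72 × 4.5 product is a separate misprint that leaves 342 unchanged and adds no weight to this point.

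**What to change.** - **Model.** Drop the free group main effect so that the arms share a baseline mean, keeping time and time-by-group. In the subgroup models keep subgroup and subgroup-by-time, and constrain the arms to be equal at baseline within each subgroup. Alternatively, model the three follow-ups with baseline and baseline-by-time as covariates.
- **Sample size text.** Replace the sentence on ignoring the longitudinal design with a power statement for the model actually used, and say whether 15 is an SD of scores or of change.
- **Misprint.** Change the product to 76 × 4.5 = 342.

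The cost is wording in two sections, settled before the analysis. Baseline values of both primary outcome instruments are already part of the planned assessments, and no extra participants are needed. Under the assumptions above, the adjusted analysis keeps LEFS interaction power at 80.9% or more whatever ρ turns out to be.

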### Outcome assessment

Outcomes will be assessed at baseline and 1, 3 and 6 months later. Outcome data will be obtained from all randomised participants, in so far as this is possible, regardless of compliance with the trial protocol. Outcome measurements will be made by an assessor blinded to allocation. The participants, as well as physiotherapists and investigators involved in the trial, will be asked to avoid giving information that could reveal participant's allocation to the blinded assessor. After each assessment the assessor will be asked if he or she was blinded to allocation and will be asked to guess which group the participant was allocated to.

At the baseline assessment, demographic and injury details will be recorded. Classification of fracture severity (severe or not severe) will be based on the number of malleoli fractured [20] and the presence of dislocation: bi- or tri-malleolar fractures and any fractures with dislocation will be classified as severe. The assessor will classify fracture severity by examining the radiology entries in the hospital records or, if these are not available, by examining plain radiographs taken before and after the fracture reduction. Two psychological scales will also be used: depression, anxiety and stress will be measured using the Depression, Anxiety, Stress Scales 21-item [24], and pain catastrophising will be assessed using the Pain Catastrophising Scale [25].

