The primary conclusions about effectiveness of rehabilitation will be based on between-group comparisons of activity limitation and quality of life at 3 months. The primary conclusions about whether fracture severity and age and gender influence the effectiveness of intervention will be based on the interactions between these factors and effects of rehabilitation for activity limitation and quality of life at 3 months.

The economic evaluation will examine differences between participants in the *Rehabilitation *and *Advice *groups in terms of costs incurred and changes in perceived activity limitation (cost-effectiveness analysis) or utility gained (cost-utility analysis). The incremental cost-effectiveness (utility) ratio (ICER) will be calculated as: ICER = (*C_R _*- *C_A_*)/(*U_R _*- *U_A_*), where C is average cost, U is the average effectiveness or utility score, and subscripts R and A denote the *Rehabilitation *and *Advice *arms. The *Rehabilitation *program can be said to be cost-effective relative to *Advice *about exercise if it (a) produces less activity limitation or greater utility at a lower cost or (b) the cost per activity limitation avoided or per quality-adjusted life years gained (i.e. the incremental cost-effectiveness (utility) ratio) is less than some threshold value (e.g. $50,000). Bias-corrected bootstrapped estimates (1,000 replications) will be used to test for the difference in mean costs and to obtain 95% confidence intervals for between-group differences in mean costs. Between-group differences in utilisation will be tested using Fisher's exact test. Sensitivity analyses will be undertaken to explore the robustness and validity of the results. Both costs and outcomes will be varied in line with results from similar studies reported in the literature and the upper and lower limits of estimates from this trial.

To establish the predictors of outcome after ankle fracture, univariate linear regression will be used to examine the relationship between seven baseline variables (fracture severity, pain, ankle range of motion, mobility, depression, anxiety and stress, and pain catastrophising) and activity limitation at 1-month and 6 months after removal of immobilisation. A multivariate linear prediction model will be developed using methods described by Harrell [32].

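### Random intercepts as the only stated dependence structure can misstate the standard error of the primary 3-month effect, in either direction; an unstructured covariance would remove the risk cheaply

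*Protocol article*

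**What the plan says.** All of this is in the protocol article.

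- **Timing (Outcome assessment).** "Outcomes will be assessed at baseline and 1, 3 and 6 months later". The visits are unequally spaced.
- **Mean model (Statistical analysis).** Baseline is an outcome row, not a covariate. Time enters as "four times, dummy-coded as three variables, with the baseline time as the referent category", with group and the three group-by-time interactions.
- **Effect estimate (Statistical analysis).** "The effect of rehabilitation at each of the three follow-up time points is estimated with the relevant interaction term". Each effect is therefore a between-group difference in change from baseline.
- **Dependence (Statistical analysis).** "The model will incorporate random intercepts to account for the dependence of repeated measures". No random slope, residual covariance or robust standard error is named, and none is excluded.
- **Primary time point (Statistical analysis).** "The primary conclusions about effectiveness of rehabilitation will be based on between-group comparisons of activity limitation and quality of life at 3 months". The conclusions on fracture severity and on age and gender also rest on 3-month interactions, from the same model with added terms.
- **Error rate (Sample size).** "In our calculations we assumed an alpha of 0.05, and we allowed for 5% loss to follow-up".

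**The concern.** A random intercept with independent, constant-variance residuals is compound symmetry: every visit has the same variance and every pair of visits the same correlation. Under that model the variance of each interaction uses one pooled within-person variance, drawn from all six pairs of visits. The primary test needs only the variance of the change from baseline to 3 months. If that change is more variable than the average pair, the interval is too narrow and the test rejects too often. If it is less variable, the interval is too wide and power is lost.

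There is reason to doubt equal correlations here. Baseline is the day immobilisation is removed, and the later visits fall during recovery. The Background reports that, in the group's earlier work, the only independent early predictors (pain and dorsiflexion range) explained just 9% to 12% of later variation in activity limitation. Weak baseline-to-follow-up correlation with strong correlation among follow-ups is therefore plausible, and that is the pattern that makes the standard error too small.

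The two 3-month main comparisons are at stake, and so are the subgroup interactions, which are a primary aim and set the recruitment target.

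**Working it through.** **Reproducing the plan's own figure.** The inputs come from Sample size: a 10-point effect on the Lower Extremity Functional Scale, SD 15, power 80%, alpha 0.05 and 5% loss. Two-sided testing is assumed. The plan's result is 38 per group, 76 in all.

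- Per group: 2 × (1.96 + 0.84)² × (15/10)² = 35.3, so 36 per group and 72 in all. 72/0.95 = 75.8, so 76.
- Inflation for interactions with k = 0.5: 2 + 0.5 + 2 = 4.5, and 76 × 4.5 = 342.

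The target reproduces from 76. (The line printed with 72 as the multiplicand would give 324. That slip has no bearing here.) The calculation uses one SD per scale and ignores the longitudinal design, so it supplies no between-visit correlation.

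**Formulae, complete balanced data, n = 171 per group.** Let D(j,k) = Var(Yj) + Var(Yk) − 2Cov(Yj,Yk).

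- Model variance of the 3-month interaction = (2/n) × mean of D over the six visit pairs.
- True variance = (2/n) × D(0, 3 months).
- With r = true/model, type I error = 2 × [1 − Φ(1.96/√r)].

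If the covariance is the same in every subgroup, the same r applies to the subgroup interactions. Both variances are then multiplied by the same function of the cell sizes.

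**One case in full** (assumed: SD 15 at every visit; correlation 0.3 between baseline and follow-ups, 0.7 among follow-ups).

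- Three baseline pairs: D = 2 × 225 × 0.7 = 315. Three follow-up pairs: D = 2 × 225 × 0.3 = 135. The mean is 225.
- r = 315/225 = 1.40.
- Model SE = √(2 × 225/171) = 1.62. True SE = √(2 × 315/171) = 1.92. The model SE is about 15% too small.
- Type I error = 2 × [1 − Φ(1.96/1.183)] = 9.8%.

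**Range.** Every correlation and visit SD below is an assumption. SDs are equal unless stated.

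| Assumed pattern | r | Type I error |
|---|---|---|
| All correlations 0.5 | 1.00 | 5.0% |
| Decay by calendar month, 0.8 / 0.9 per month | 0.99 / 0.95 | 4.9% / 4.4% |
| All correlations 0.5, SDs 12, 15, 15, 15 | 0.91 | 4.0% |
| All correlations 0.5, SDs 15, 15, 12, 10 | 1.05 | 5.6% |
| Decay by visit order, 0.5 to 0.7 | 1.16 to 1.19 | 6.9% to 7.2% |
| Baseline 0.4, follow-ups 0.6 | 1.20 | 7.4% |
| Milder graded: baseline 0.5, 0.4, 0.35; follow-ups (1–3, 1–6, 3–6 months) 0.65, 0.55, 0.75 | 1.29 | 8.4% |
| Graded: baseline 0.5, 0.3, 0.2; follow-ups 0.6, 0.5, 0.8 | 1.35 | 9.2% |
| Baseline 0.3, follow-ups 0.7 | 1.40 | 9.8% |
| Baseline 0.3, follow-ups 0.8 | 1.56 | 11.6% |
| Baseline 0.2, follow-ups 0.8 | 1.60 | 12.1% |

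**Weak baseline correlation and a smaller baseline SD together.** With baseline SD 12 and the others 15, the graded pattern falls from 9.2% to 8.1% and the milder one from 8.4% to 7.3%. With baseline SD 10 they fall to 7.4% and 6.7%.

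**Checks.** In 20,000 simulated trials of 171 per group, the random-intercept test rejected in 5.0% with all correlations 0.5, 9.9% for 0.3/0.7 and 11.3% for 0.3/0.8. A test that left the covariance free rejected in 4.8% to 5.2% in every scenario simulated. One mixed-model fit to data generated under 0.3/0.7 gave a model SE of 1.60, against 1.88 from the change scores in the same data and 1.92 in truth.

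**The case against.** The strongest reply is that neither direction nor size is established. This stands. The document gives one SD per scale and no correlation between visits. The standard error is exactly right under compound symmetry and too large under some other patterns. The 9% to 12% figure concerns pain and dorsiflexion range. The text does not say whether baseline activity limitation was among the eight candidate variables, and nothing comparable is given for quality of life.

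A second reply is that if function at baseline is uniformly poor, the baseline SD is smaller, which pulls the error rate down. This also stands, although in the two graded examples the rate stays above 5%. The Background gives a mean of 33.6 out of 80 from the earlier study and no SD, so the premise is itself unverified.

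A third reply is that the article does not say random intercepts are the whole structure, and that residual covariance is often left to an analysis plan. This stands in part: the sentence is compatible with a richer residual model. But it names one device and gives it the job of handling the dependence, so an analyst who follows it would fit compound symmetry. The point concerns a stated choice, not missing detail.

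A reader might infer that the 3-month standard error is wrong as planned, or that the type I error will nearly double. The document supports neither. A rate of 10% needs r of about 1.42, which lies in the upper part of the range and depends on correlations that are not given.

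**Conclusion.** The concern holds as a conditional one. Read plainly, the stated structure ties the standard error of the primary 3-month effect, and of the primary subgroup interactions, to an equal-variance, equal-correlation assumption that nothing in the document supports. Over the patterns tried, the nominal 5% test has a true type I error of about 4% to 12%. The Background makes the inflating pattern plausible but does not establish it.

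The limits are clear. With complete data the estimated effects do not change, only their standard errors. Ankle range of motion, pain and walking speed are measured only at baseline and 1 month, so there is a single visit pair and the contrast variance is correct. The figures assume complete balanced data, a two-sided test, model-based standard errors and residuals that are independent with constant variance.

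**What to change.** For every continuous outcome measured at more than two visits, replace the random-intercept structure with an unstructured covariance across visits, with Kenward-Roger or Satterthwaite degrees of freedom. State in advance that, if the model does not converge, the mean model is kept and participant-level robust standard errors are used. Apply the same structure in the fracture-severity and age/gender models. If the analysis plan already specifies this, the article's sentence should be read with it.

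The cost is small. Four visits need 10 covariance parameters against 2 for a random intercept, with up to 342 × 4 = 1,368 observations. The downsides are those few extra parameters and possible use of the fallback. The mean model, the effect estimates and the sample size stay as they are, and the protection works whichever way the standard error would otherwise have been off.

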### Economic evaluation

The economic evaluation will consist of cost-effectiveness and cost-utility analyses. Costs will be measured in terms of direct costs to the health system and out-of-pocket costs to the participants over a 6-month period, and collected in a questionnaire at the 1, 3 and 6 month follow-up period. From an economic perspective, costs are measured by resource use. This allows the identification of the opportunity cost of resources used, that is, what could have been achieved had those resources been allocated to the best alternative use. In this trial the costs of the interventions and any out-of-pocket costs incurred by participants will be identified, measured and valued. Table 2 indicates the type of resources which will be captured, the sources of data, and proposed methods of valuation.

**Table 2 T2:** Assessment of resource use.

Type of resource	Method of assessment	Method of valuation
Physiotherapists' time	Physiotherapists' report	Salary rates plus on-costs for physiotherapists using published prices
Equipment	Questionnaires at 1, 3, 6 months	Manufacturer's price (depreciated over 3 years)
Medication, visits to general practitioners and other health professionals, hospitalisation, visits to emergency department	Questionnaires at 1, 3, 6 months	Published prices (e.g. Pharmaceutical Benefits Scheme and Medicare Benefits Schedule reimbursement) and/or actual costs to participants
Visits to community services or alternative or complementary health practitioners	Questionnaires at 1, 3, 6 months	Actual costs to participants

The cost-effectiveness analysis will use the Lower Extremity Functional Scale [26] as a measure of effectiveness. The cost-utility analysis will use the Assessment of Quality of Life instrument as a measure of utility.

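### The economic evaluation is described as comparing changes, but the ICER formula uses average scores with no baseline term, so its denominator is inconsistent with the trial's effect estimate and less precise than it could be

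*Protocol article*

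**What the plan says.** All of this is in the Protocol article.

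- **Statistical analysis, economic paragraph.** The arms are to be compared on costs and on "changes in perceived activity limitation (cost-effectiveness analysis) or utility gained (cost-utility analysis". The next sentence gives the ICER as (C_R - C_A)/(U_R - U_A), where "C is average cost, U is the average effectiveness or utility score".
- **Economic evaluation.** "The cost-effectiveness analysis will use the Lower Extremity Functional Scale" as its measure of effectiveness; AQoL is the measure of utility.
- **Statistical analysis, first paragraph.** The clinical effect comes from a mixed model with time dummy-coded "with the baseline time as the referent category". "The effect of rehabilitation at each of the three follow-up time points is estimated with the relevant interaction term". That is a difference in change from baseline.
- **Decision rule.** Rehabilitation counts as cost-effective if it "produces less activity limitation or greater utility at a lower cost", or if the ratio falls below a threshold value. Both limbs depend on the sign of the denominator.
- **Randomisation.** Allocation is stratified by site only, so baseline LEFS and AQoL are balanced only by chance.

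**The concern.** A change and a score are different quantities, and the article uses one in the sentence that sets up the comparison and the other in the formula. Nothing shown subtracts baseline from U or adjusts for it. Taken as printed, the LEFS ratio would not divide by the effect that the same section reports as the effect of rehabilitation.

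Two things are at stake. First, the effectiveness and cost-effectiveness results could point in different directions when the effect is small. Cost-effectiveness is part of primary aim (a), so the mismatch would be visible and awkward to explain. Second, the baseline measurements are collected anyway, and leaving them out of the denominator gives up precision.

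**Working it through.** **Inputs.** From Sample size: LEFS SD 15, target difference 10, alpha 0.05, 5% loss, 171 per arm. Assumed, because the article does not give them: baseline-to-follow-up correlation r (0.3 to 0.5, with 0.1 to 0.7 as a wider check) and the same SD of 15 at baseline and follow-up.

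**The plan's own figure.** The article claims "an 80% probability of detecting a difference between the group means of 10 points" with 38 per group. Two-sided, n = 2 × (1.96 + 0.842)² × 15²/10² = 35.3, so 36 per arm. Allowing for loss, 36/0.95 = 37.9, so 38 per arm or 76 in all. The inflation factor is 2 + 0.5 + 2 = 4.5, and 76 × 4.5 = 342. The figure reproduces. (The printed product starts from 72, which would give 324; that slip has no bearing here.)

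**The identity.** Let F be the between-arm difference in mean follow-up score, B the difference at baseline, and C = F - B the difference in mean change. With complete data, C is what the time-by-group interaction estimates. The printed denominator is F = C + B.

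**Size of B.** SE(B) = 15 × √(2/171) = 1.62 points, a 95% range of about ±3.2. An imbalance of 2 points or more in either direction has probability about 0.22.

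**Illustration (all values assumed).** Baseline means are 32.6 (Rehabilitation) and 34.6 (Advice); 3-month means are 60 and 61. Then F = -1 and C = (60 - 32.6) - (61 - 34.6) = +1. With an assumed extra cost of $300, the formula gives -$300, with Rehabilitation dominated. The wording in the text gives +$300 per LEFS point.

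**How often F and C have opposite signs.** After 5% loss, 171 × 0.95 gives 162 per arm, so SE(F) = 15 × √(2/162) = 1.67. Simulating from a bivariate normal distribution:

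| True effect (points) | r = 0.3 | r = 0.5 | range over r = 0.1 to 0.7 |
|---|---|---|---|
| 1 | 25% | 27% | 23-29% |
| 2 | 16% | 15% | 14-16% |
| 3 | 7% | 6% | 4-9% |
| 5 | 0.6% | 0.2% | 0.1-1.3% |
| 10 | about 0% | about 0% | about 0% |

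**Effect on cost per point at the planned effect.** B and C are negatively correlated. Given an observed change effect equal to a true effect of 10, B has mean 0 and SD = SE(B) × √((1 + r)/2).

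- r = 0.3: 1.62 × √0.65 = 1.31, so ±2.56. The ratio 10/12.56 is about -20%, and 10/7.44 is about +34%.
- r = 0.5: 1.62 × √0.75 = 1.40, so ±2.75. The ratio 10/12.75 is about -22%, and 10/7.25 is about +38%.

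**Precision of the candidate denominators (162 per arm).**

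| Contrast | Formula | r = 0.3 | r = 0.5 |
|---|---|---|---|
| Raw score | s = 15√(2/162) | 1.67 | 1.67 |
| Change | s√(2(1 - r)) | 1.97 | 1.67 |
| Baseline-adjusted | s√(1 - r²) | 1.59 | 1.44 |

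**The case against.** **A consistent reading exists.** The formula sits between a sentence about changes and utility gained and one about limitation avoided and quality-adjusted life years gained. U is one symbol serving two ratios, so average effectiveness could mean average change. The article is also a condensed account, and details of baseline adjustment are often left to an analysis plan. This has weight, but the article chose to print a formula and define its terms. The word used there is score, and the measure named elsewhere is the LEFS itself. The conflict is in what is stated, not in what is left out.

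**A reader might infer that the formula biases the ICER, or gets its sign wrong in a quarter of trials.** The documents do not support that. Under randomisation F and C estimate the same effect without bias. The percentages above are disagreement between two noisy estimators, not the error rate of one. At a true effect of 1 point, the raw difference has the wrong sign in about 27% of trials; the change contrast has it in about 31% (r = 0.3) or 27% (r = 0.5). Change scores are therefore not the more accurate standard in this range.

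**A reader might also infer a swing of -24% to +47% in cost per point** by moving B over its full ±3.2 while holding the change effect at 10. That ignores the negative correlation between B and C; the conditional figures above are the fair ones.

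**Reversal matters only for small effects.** The Sample size section regards differences below 10 LEFS points as unlikely to be clinically worthwhile, and near zero any ICER has an unstable sign. This stands and limits the weight of the point. Small effects cannot be ruled out, though: the Background reports that the one earlier trial of an exercise program against usual care found no overall benefit.

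**Conclusion.** The point holds as an inconsistency with a modest cost in precision. The text and the formula define different denominators, and the printed one leaves out baseline data that the trial collects. It is not a source of bias. Conflicting signs are a realistic prospect only at true effects of about 3 LEFS points or less, and practically absent at the planned 10. At 10 points, cost per point under the two definitions would still differ by roughly -20% to -22% or +34% to +38% at the 95% limits.

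These figures rest on the plan's SD of 15 applied at both times, 162 to 171 per arm, and an assumed correlation of 0.3 to 0.5. The article gives no correlation and no SD for the utility score, so the size for the cost-utility ratio cannot be worked out in the same way. The inconsistency applies to it equally.

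**What to change.** Replace the definition of U with one sentence: U_R - U_A is the baseline-adjusted between-group difference in LEFS, and for the cost-utility ratio the difference in utility gained adjusted for baseline AQoL. If the ICER itself is bootstrapped, re-estimate the adjustment within each replicate. At 162 per arm this lowers the SE from 1.67 to about 1.59 (r = 0.3) or 1.44 (r = 0.5).

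This contrast is not numerically the planned time-by-group interaction, so the plan must also say how the two analyses relate. There are two options:

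- Use the same baseline-adjusted contrast in both the effectiveness and the economic analysis. This gives consistency and precision, but it changes the stated effectiveness model.
- State that the ICER denominator is the interaction estimate. This restores consistency, but at r of 0.5 or less it is no more precise than raw scores.

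The cost is one sentence and slight extra analysis. Both instruments are already measured at baseline, so no new data are needed.
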